***Outcome measures***

Data will be collected from the intervention and control group at baseline, and immediately after the completion of the intervention. All the instruments will be administered in English language which is the medium of instruction for the intervention.

*Self-efficacy for coping with cancer*

Self-efficacy for coping with cancer will be measured with the Cancer Behavior Inventory-Brief Version (CBI-B). The instrument comprises 12-items measuring confidence of individuals in performing activities that show how well they are coping with the demands of cancer and their treatment. Each item will be scored on a nine-point Likert scale with ‘1’ meaning ‘not at all confident’ and ‘9’ meaning ‘totally confident’. Higher scores indicate greater self-efficacy in coping. This instrument has been used in BC studies. It has also been validated and found reliable with a Cronbach’s α coefficient ranging from .84 to .88. (Heitzmann, 2001). (See Appendix C).

*Coping*

Coping will be assessed with Coping Orientation to Problems Experienced Inventory (Brief COPE). The scale can measure primary coping styles under three subscales: problem-focused coping, emotion-focused coping and avoidant coping. This 28-item instrument was developed as a short version of the original 60-item COPE scale (Carver et al., 1997). The 28 items are measured on a four-point scale (ranging from1= I haven’t been doing this at all, 2= a little bit, 3= a medium amount, and 4= I’ve been doing this a lot). The instrument has also been verified among patients with breast cancer receiving chemotherapy and have a fairly good reliability and validity. Internal consistencies ranged from 0.25 to 1.00, and intraclass correlation coefficient ranged between 0.05 and 1.00 (Yusoff et al., 2010). (See Appendix D).

*Anxiety and Depression*

Anxiety and depression will be assessed with the Hospital Anxiety and Depression Scale (HADS). The instrument has been used to measure anxiety and depression in BC patients. HADS comprises anxiety and depression subscales with seven items per subscale. A total score of 0-7 is normal, 8-10 is borderline abnormal and 11-21 is abnormal. This instrument has been validated and also found to be reliable with a Cronbach’s α coefficient of 0.79 for the anxiety subscale, 0.87 for the depression subscale, and 0.85 for all the items in an investigation into the psychometric properties in a previous study among BC patients (Rodgers et al., 2005) (See Appendix E).

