***Sample size planning***

Sample size is calculated based on the primary outcome of self-efficacy. Power analysis was done with G*Power version 3.1 (Faul et al., 2007), and a medium effect size of 0.53 which was demonstrated in a previous mHealth psychoeducational study featuring women undergoing BC chemotherapy. Power was 0.8 and *p*<.05 with 10% attrition which was an average attrition rate found from a recent mhealth systematic review conducted on this population (Cohen 1988; Zhu et al., 2018). Sample size is estimated to be 126 participants, but the exact number will be confirmed after the pilot study.

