**Outcomes measures**

The outcome measures will be the same as described in the pilot study.

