**Data analysis**

SPSS version 25 will be used to analyse quantitative data. The demographic data and clinical data will be analysed through descriptive statistics including frequencies, percentages, mean and standard deviation. Continuous variables at baseline, and immediately after the intervention will be compared through independent samples t- test for the continuous variables and chi-square or Fisher’s exact test for the categorical variables where appropriate. Primary and secondary outcomes data will be analysed through the generalized estimating equation (GEE) model provided the assumptions for homogeneity of variance and normality are met (Bell et al., 2014). In a bid to control for attrition bias, the intention-to-treat principle will be used to account for loss to follow up (Nam & Toneatto, 2016).

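### Intention to treat is named as the remedy for loss to follow-up, but it supplies no missing outcomes, and the unspecified GEE could be biased if dropout is informative and differs by arm

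*Protocol*

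**What the plan says.** In the Protocol's main-trial Data analysis section, the sentence on attrition reads: "In a bid to control for attrition bias, the intention-to-treat principle will be used to account for loss to follow up". The same section gives the model: "Primary and secondary outcomes data will be analysed through the generalized estimating equation (GEE) model". It names no working correlation, weighting, imputation or missingness assumption.

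The timing comes from Outcome measures in the pilot part: "Data will be collected from the intervention and control group at baseline, and immediately after the completion of the intervention". The main trial takes this over: "The outcome measures will be the same as described in the pilot study". There is therefore one measurement after baseline.

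Sample size planning allows for "with 10% attrition which was an average attrition rate found from a recent mhealth systematic review", arrives at 126 women, and gives no split of attrition by arm.

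**The concern.** The sentence treats two separate matters as one. Intention to treat is a rule about the analysis set: every randomised woman counts in the arm she was allocated to. Loss to follow-up is a missing-data problem, and the rule does not solve it. A woman who misses the only post-intervention assessment has no outcome and no intermediate visit to borrow from. Keeping her in her arm leaves that cell empty.

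What happens to her then depends on the model. The post-intervention t-test listed in the same section drops her. A GEE with independent working correlation uses only her baseline score, so the post-intervention means come from completers alone. A GEE with exchangeable correlation uses her baseline to inform the post-intervention mean. The protocol does not say which applies.

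At stake is the arm difference in self-efficacy. If low scorers leave more often, and one arm loses more of them, a completer-type comparison favours the arm with the heavier loss. The bias can run either way.

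**Working it through.** **1. The plan's own figure.** Inputs from Sample size planning: effect 0.53, power 0.80, alpha 0.05 (two-sided assumed; sidedness is not stated), attrition 10%. Normal approximation:

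n per arm = 2 × (1.960 + 0.842)² / 0.53² = 55.9, so 56; 56 / 0.90 = 62.2, so 63; total 126.

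The t-test version gives 57 per arm, and 114 × 1.1 = 125.4, again 126. The stated 126 reproduces.

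**2. Women without an outcome.** 126 × 0.10 = 12.6, about 13 lost and 113 with a post-intervention score.

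**3. When bias arises.** Take SD 1 and baseline–post correlation r. Let m(p) be the mean baseline score, in SD units, of the women who remain when a share p drops out. If dropout depends on baseline only, an analysis that ignores baseline has

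bias = r × [m(p intervention) − m(p control)].

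- Dropout random within arm: m(p) = 0 at any p, so bias is 0 even with unequal rates. Large-sample simulation at 15% vs 5% and 20% vs about 0% gave at most 0.005 SD.
- Equal rates and the same mechanism in both arms: the two terms cancel and bias is 0.
- Dropout linked to baseline and unequal: the terms differ and bias remains.

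**4. Illustrative size.** Assumptions not in the protocol: r = 0.5; the log-odds of dropout rise by 1 or 1.5 for each SD of lower baseline self-efficacy; overall dropout 10%, split as shown (intervention vs control).

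| Split | Slope | m (intervention) | m (control) | Bias = 0.5 × difference | Share of 0.53 |
|---|---|---|---|---|---|
| 15% vs 5% | 1 | 0.133 | 0.047 | 0.043 | 8% |
| 15% vs 5% | 1.5 | 0.175 | 0.065 | 0.055 | 10% |
| 18% vs 2% | 1 | 0.157 | 0.019 | 0.069 | 13% |
| 18% vs 2% | 1.5 | 0.206 | 0.028 | 0.089 | 17% |
| 10% vs 10% | 1 | 0.091 | 0.091 | 0 | 0% |

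The bias is proportional to r. With r from 0.3 to 0.7, the four unequal rows span about 0.03 SD (0.3 × 0.086) to 0.12 SD (0.7 × 0.178). Swapping the arms reverses the sign.

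**5. Does the choice of fit matter?** Simulation with no true effect, 63 per arm, r = 0.5, slope 1.5, 400 trials per scenario (Monte Carlo SE 0.009):

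| Split | GEE independence | GEE exchangeable | Baseline-adjusted |
|---|---|---|---|
| 16% vs 4% | +0.066 | +0.002 | −0.001 |
| 18% vs 2% | +0.091 | +0.008 | +0.002 |
| 10% vs 10% | −0.007 | −0.005 | −0.005 |

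Using baseline removes the bias when baseline drives dropout.

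**6. Dropout driven by the unseen outcome.** At slope 1, the bias at 15% vs 5% is about 0.09 SD (independence) and 0.07 SD (exchangeable). At 20% vs about 0% it is 0.17 and 0.13 SD. Using baseline reduces this bias but does not remove it.

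**The case against.** Several counter-arguments carry weight.

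- *A reader might infer that unequal dropout by itself biases the result.* It does not. With dropout random within arm, even 20% against almost none left no bias. The dropout must be related to baseline or outcome and also differ by arm.
- *A reader might infer that the planned GEE is biased by 0.07 to 0.09 SD.* The protocol does not support that either. It names no working correlation, and with an exchangeable one the bias from baseline-driven dropout is about nil. The splits, slopes and correlation are assumptions; only the overall 10% is in the protocol. Even 0.09 SD is under half the standard error of the unadjusted arm difference, √(2/56.7) = 0.19 SD.
- *Differential dropout is not established.* Women are unblinded and only one arm has weekly sessions, but controls receive standard care with education at clinic visits. Outcomes are collected at the clinic, so a woman who stops using the app need not lose her outcome.
- *The t-test is secondary to this argument.* The primary outcome is assigned to the GEE.
- *Missing-data detail usually belongs in the SAP, which is not at hand.* That is right for the working correlation, the imputation model and sensitivity analyses, and their absence from the protocol is not the fault raised here.

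None of this rescues the attrition sentence. It assigns intention to treat a task it cannot perform, and a SAP that carried it forward faithfully would carry the error too.

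**Conclusion.** The point holds in a conditional form. The protocol is wrong to present intention to treat as the control for attrition bias: with one post-intervention measurement it supplies nothing for the roughly 13 women expected to be lost. Ordinary unweighted GEE does not fill the gap by default, since it is in general valid only when dropout is completely random given arm. The primary result could be biased, in either direction, if dropout is both informative and different between arms.

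The size cannot be fixed from the protocol, because attrition by arm is not given. On the stated assumptions it is about 0.05 SD at 15% versus 5% and 0.07 to 0.09 SD at 18% versus 2% for an analysis that ignores baseline, and about zero for one that uses it. If dropout depends on the unseen outcome, some bias remains under any missing-at-random method. The statement should be corrected before outcome data are seen; neither the design nor the sample size is called into question.

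**What to change.** Replace the attrition sentence with wording such as: *All randomised women are analysed in their allocated arm. The primary analysis is valid under missing at random and uses baseline CBI-B.* Then name one method:

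- a likelihood-based mixed model that includes baseline;
- multiple imputation by arm, followed by the planned GEE; or
- as a minimum, the GEE with the baseline measurement included and an exchangeable working correlation.

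Add one sensitivity analysis for outcome-dependent dropout, for example a delta adjustment that shifts the imputed scores in the unfavourable direction.

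The cost is a change of wording and slightly more analysis work on data already planned. No extra data collection is needed and the sample size of 126 is unaffected.

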**Ethical considerations**

The ethical principles of the Declaration of Helsinki (World Medical Association, 2013) will be adhered to in this study. Ethical approval will be sought from the Joint Chinese University of Hong Kong-New Territories East Cluster Clinical Research Ethics Committee and the study settings in Nigeria. Approval to use the instruments will be obtained from the original authors. All through the phases, the research assistants will administer an information sheet containing detailed information about the study and they will complete a consent form afterwards.

The participants will be assured that the data collected will be used solely for the research and they will also be given a chance to ask questions and make clarifications. They will also be informed that they do not need to pay to use the application. Similarly, they will be assured that participation is voluntary and their decision to participate or otherwise will not affect their treatment. Similarly, they will be assured of confidentiality through the study.

During interaction on the mobile app, the participants will be free to use a name they are comfortable with or remain anonymous so their identity can be confidential. They will also be informed not to share the details of their interaction with anybody who is not part of the intervention to maintain privacy. Furthermore, they will not be required to display their personal pictures. Sensitive issues will not be raised during the interaction on the application. The application will not made available on social networking sites or public domains. Each participant will be given a unique link to download the application. After download, the link will be revoked. Each participant will create a unique username and password which they will be instructed not to share with any other person. They will be able to change the password anytime they desire. Data from the app will be encrypted and will only be accessible to the principal investigator and software engineer. The participants will be informed that the principal investigator and software engineer can access their profile. The principal investigator and the software engineer will be responsible for safekeeping of the data from the application during the study. Other study data will be safely kept by the principal investigator. The software engineer will transfer the data from the application to the principal investigator and supervisor after the study. The principal investigator will be responsible for keeping all study data in a locked cabinet after the study. All paper copies of the data will be destroyed by a paper shredder and all electronic copies will be permanently deleted from the computer and storage devices by the principal investigator five years after the study is completed and published. Principles of beneficence, non-maleficence, and trust will be upheld throughout the study.

**Impact of the study on Nursing Practice**

As the usage of mHealth in this population is relatively new and with very limited evidence; this study, which to the best of the researcher’s knowledge is the first in Nigeria, will provide evidence for the integration of mHealth into BC chemotherapy. Similarly, nurses will be informed about the effectiveness of mPEI for this population. Finally, it is hoped that the psychological concerns of Nigerian women with BC will be adequately addressed while receiving chemotherapy.

